## Abstract

**Background:**

There is increasing interest among older people in moving into retirement villages (RVs), an attractive option for those seeking a supportive community as they age, while still maintaining independence. Currently in New Zealand there is limited knowledge of the medical, service supports, social status and needs of RV residents. The objective of this study is to explore RV facilities and services, the health and functional status of RV residents, prospectively study their healthcare trajectories and to implement a multidisciplinary team intervention to potentially decrease dependency and impact healthcare utilization.

**Methods:**

All RVs located in two large district health boards in Auckland, New Zealand were eligible to participate. This three-year project comprised three phases: The survey phase provided a description of RVs, residents’ characteristics and health and functional status. RV managers completed a survey of size, facilities and recreational and healthcare services provided in the village. Residents were surveyed to establish reasons for entry to the village and underwent a Gerontology Nurse Specialist (GNS) assessment providing details of demographics, social engagement, health and functional status. The cohort study phase examines residents’ healthcare trajectories and adverse outcomes, over three years. The final phase is a randomised controlled trial of a multidisciplinary team intervention aimed to improve health outcomes for more vulnerable residents.

Residents who triggered potential unmet health needs during the assessment in the survey phase were randomised to intervention or usual care groups. Multidisciplinary team meetings included the resident and support person, a geriatrician or gerontology nurse practitioner, GNS, pharmacist and General Practitioner. The primary outcome of the randomised controlled trial will be first acute hospitalization. Secondary outcomes include all acute hospitalizations, long-term care admissions, and all-cause mortality.

**Discussion:**

This paper describes the study protocol of this complex study. The study aims to inform policies and practices around health care services for residents in retirement villages. The results of this trial are expected early 2020 with publication subsequently.

**Trial registration:**

Australia and New Zealand Clinical Trials Registry: ACTRN12616000685415. Registered 25.5.2016.

**Universal Trial Number (UTN):** U111–1173-6083.

## Background

The retirement village (RV) industry provides an attractive housing option for older people who seek a supportive community while still maintaining independence as they age [1]. The term “Retirement Village” in New Zealand (NZ) is also known internationally as a Continuing Care Retirement Community (CCRC), defined as full range lifetime of care from independent to assisted living. The term RV is legally defined in accordance with NZ’s Retirement Villages Act 2003 as “part of any property, building or other premises that contains two or more residential units that provide, or are intended to provide residential accommodation together with services or facilities or both, predominantly for persons in their retirement and their spouses or partners” [2].

There has been a significant growth in RVs in NZ as well as internationally in high resourced countries. From 1988 to 2008, the population of people over 85 years has more than doubled in Auckland, NZ [3]. In spite of this, long-term care (LTC) beds for those requiring 24-h care decreased by almost a third during this same time period, likely due to government policies that promoted community care and “ageing in place” [3–5]. This is likely to have resulted in a trend of increased physical dependency and healthcare complexity for those currently living in RVs [6, 7]. During this same time period, the RV sector saw enormous growth. Recent estimates indicate that there are 380 registered RV complexes in NZ, with 390,000 occupants, a three-fold increase from 1998. Between 2010 and 2016, 40 new RVs opened – a growth rate of 12%. There were almost no RV residents in NZ in the late 1980s, yet by 2017 an estimated 12.6% of people of 75 years and over in NZ lived in RVs [8].

Aside from ‘ageing in place’ and the overall ageing of the population, there are a number of drivers responsible for the increase in demand for RV units (villas/apartments). RV living is growing in popularity with an increasing range of housing and lifestyle ‘products’ to choose from and providing an alternative to traditional lower level residential aged care. Other influences include NZ’s recently strong local housing market and the relative affordability of RV living, and a decline in alternative accommodation options (such as the decline in ageing parents living with their children) [8].

Internationally, RVs have been shown to impact positively on residents’ wellbeing, with higher quality of life compared to those living in family homes or in LTC [9, 10]. NZ research has shown that RV residents are more educated, have more financial resources and better well-being, but have significantly greater functional dependency compared with those in private dwellings [11]. It is clear that only those with substantial financial resources can afford the significant personal investment required initially (NZ$250,000– NZ$1 M+) and the (usually) on-going monthly service fees, [8] resulting in inequity in access.

An increase in the ageing population in NZ is projected over the next decade. The number of older people living within RVs will also likely increase, who as they age will be more prone to increased frailty, greater health needs and declining independence. Indeed, it is likely that RV residents may include a proportion of frailer dependent older people that would have previously resided in LTC facilities [4, 5]. However, little is known in NZ, or elsewhere, about health or functional needs of this potentially vulnerable group of older people, or of what services are or are not provided by RVs to their residents.

In 2012 we completed a small feasibility survey of the functional status, dependency & social circumstances of 110 participants in Auckland RVs [12]. Forty-five percent had been assessed for publicly funded homecare help while 15% received help with personal cares. They had higher morbidity and need (vs. community-dwelling older people), including falls, general health, help with bathing/ dressing, and cognition. These findings suggest that physical function of RV residents lies between those living in private homes and those in LTC.

The basis for the current study was our belief that RV residents may have multiple unmet needs together with declining medical and functional ‘trajectories’ with time, and that a targeted intervention might decrease the risk first acute hospitalisation, number of all acute hospitalisations, LTC admissions and all-cause mortality.

The current study draws on the information gathered from residents themselves, from their healthcare records and at a facility level, to gain an overall better understanding of residents’ health status and of RV service provision. It will inform understanding of characteristics, functional abilities, medical acuity and ‘trajectories’ (actuality and time scales of hospitalisation, move to LTC, mortality) of RV residents. This will, in turn, inform health planning to improve health outcomes in residents. The aims of the current paper are to provide an overall description of the overarching project and detailed methods information.

## Methods/design

### Objectives

We hypothesize RV residents have multiple unmet needs and high healthcare use and that a targeted intervention will decrease the risk of first acute hospitalisation, number of all acute hospitalisations, LTC admissions and all-cause mortality.

The objectives of the study are:
To describe general health and functional status of residents;To describe the types of facilities and services that RVs provide;To examine the healthcare service utilization trajectories of RV residents over a three-year period (or longer depending on further funding);To assess in a randomised controlled trial (RCT) the effect of a multidisciplinary team (MDT) intervention on healthcare outcomes in an identified, at-risk subgroup of RV residents.

### Study design

This is a three-year project with data collection commencing in July 2016. This study comprises three phases: Survey phase - a description of RVs and of residents’ characteristics and health and functional status; Cohort study phase - modeling of residents’ health care trajectories up to 3 years (and longer if further funding can be secured); An RCT of a MDT intervention in the most vulnerable cohort of residents, aiming to reduce adverse outcomes. The study was approved by the New Zealand Health and Disability Ethics Committee (Ref 16/CEN/34).

#### Setting

A list of all RVs in the Auckland (ADHB) and Waitematā (WDHB) District Health Boards (that are responsible for providing and/or funding the provision of health services in their defined geographical area) was compiled from a variety of sources (online, previous study data and personal contacts). This list was used as the sampling framework for the recruitment of RVs and we planned that all RVs would be invited to take part regardless of size, ownership or location.

### Recruitment procedures

We planned to approach all RVs in ADHB and WDHB, with random sampling of units/apartments in each village using the villages’ own lists as the sampling frame. Exclusions: refusal of, or inability to consent (Addenbrookes Cognitive Examination Revised ACE-R) [13] under 65, or any resident that our research gerontology nurse specialists (GNSs: [name]) or the resident’s RV manager felt may lack capacity to consent. Ethics approval did not require written consent from the facility.

#### Village managers

A GNS allocated to each DHB contacted individual RV managers and gained verbal or email agreement for them to participate in a Village Management Survey. The purpose of this survey is to describe the RVs in the region, in terms of size, facilities and services provided, in order to give a detailed overview of the physical environment: the number of independent-living units or apartments, and ‘serviced apartments’ (units whose residents were able to access from the RV, at additional cost to themselves or to their DHB, services ranging from household help to personal care), recreational facilities accessible to residents, and healthcare services on site.

Where necessary, the Principal Investigator ([name]) contacted the Chief Executive Officers (CEOs) of large RV chains to explain the study and seek permission and access to the RV to improve the participation rate of RV managers and residents.

#### Village residents

Survey phase: We planned to access residents via RV managers, and to contact residents by letter-drop and door-knock. In smaller RVs (*n* ≤ 60 units/apartments), we planned to invite all residents to assess eligibility, whilst in larger RVs we planned to invite residents in a random sample of units (aiming for about 30 residents per RV).

Potential participants were approached using a variety of methods including letter-drop, RV newsletter, noticeboards, and resident meetings and, in larger villages, lists of units from village RV managers for random selection.

RCT resident recruitment: We planned to utilise the InterRAI Community Health Assessment (CHA) (https://www.interrai.org/community-health.html) [14] as a component of the assessment of residents in the Survey phase and to identify residents eligible for the RCT based on these data [15, 16].

As the study evolved and progressed, recruitment issues and other practical problems necessitated changes in the originally designed and funded protocol. These pragmatic changes are detailed in Table 1. Problems and issues specific to subject recruitment will form the subject of a separate publication.

**Table 1 Tab1:** Summary of planned and actual study design and conduct

	**Planned /expected**	**Implemented /actual**
**Survey Phase:**		
Village sampling frame	Sampling frame would be complete except for new villages opening during the study period and additional units opening in existing villages .	Some villages duplicated in list; and some villages listed were out of area. Villages closed units for renovation, or added units/apartments Facilities were listed that were not retirement villages. The details were updated during the course of the Survey phase.
Village selection	No selection of villages was planned. All villages would be approached, and we expected any decline in participation to be minor.	Slower than anticipated study progress led to recognition that not all villages could be included, A change in policy saw villages being recruited in random order after Dec 2017.
Village recruitment	Gate-keeping role of village managers was recognised, but the extent research team were not given permission to recruit at all was not anticipated.	A high proportion of managers declined participation early in study. This will be detailed in a separate paper.
Unit sampling frame	Within each village we anticipated that a list of all units/apartments (without names of residents) would be provided by village manager, enabling random selection of units, together with permission and security access for door-knocks and letter-drops allowing recruitment to proceed.	Some Managers declined to provide a list of units and also to permit access to doors, making door-knocks or even letter-drops impossible. Instead, these managers permitted study nurses to present an outline of the study at a residents’ meeting, and seek volunteers for participation. This will be detailed in a separate paper as above.
Call-backs	Where at door-knock there was no response, the researchers were to call back up to 5 times, in accordance with Good Practice in Conduct and Reporting of Survey Research [17]. to avoid bias towards those who are frequently at home.	After several months of fieldwork, 10 call-backs was deemed too high a number for the yield provided, and call-backs were reduced to 3.
Resident eligibility criteria	All residents in randomly-selected units would be invited to participate. Further, *every* resident under an LTC contract (i.e. receiving formal publicly-funded LTC services) would be included.	All residents in each randomly-selected unit/apartment were invited. In villages where random selection was not undertaken, all residents were invited. Few residents were in receipt of LTC contracts, and the numbers did not justify continuing this line of enquiry.
Resident sampling	Where more than one resident was in a unit/apartment, and both met resident inclusion criteria, then both were to be invited, to enable assessment of support from co-residence and inter-dependence.	This went to plan.
Informed consent	All residents were eligible to participate regardless of health or occupancy status. For those without capacity to consent but with a legal proxy available, we planned to use the combination of respondent and proxy.	On the basis of the NZ legislation, the ethics committee approval for the study did not permit recruitment of residents who did not have capacity to consent. This will be detailed in a separate paper as above.
Survey instrument(s)	Both feasibility and pilot studies used questionnaires based on our prior research in residential care facilities, based on Booth questionnaire, BRIGHT study and ARCHUS tools.	Mandatory introduction of the interRAI tool nationally was deemed more relevant, appropriate and thorough than our instruments, so the interRAI CHA was added. We selected the interRAI CHA tool (previously unused in NZ) as our main study instrument, and adapted the trialled survey tool as a supplementary survey questionnaire to capture additional items such as reasons for moving into a RV.
Timeline	We planned to begin the Survey phase recruitment on 06June 2016 and complete it by August 2018.	We began Survey phase recruitment on 27 July 2016 and completed in late August 2018.
Sample size and Power calculations	Refer to text.	Refer to text.
Data availability and collection	Survey data were expected to be collected online and immediately available for use in monitoring progress, conducting follow-up and to determine eligibility for the RCT.	Once the decision was made to use an interRAI instrument (where data are captured online and available only occasionally to researchers), it was impossible to use interRAI data directly for determining eligibility for Phase 3. Selected variables were therefore entered into the survey database for this purpose.
**Cohort Follow-up:**		
Timeline	From June 2016 to August 2018	From July 2016 to January 2020
Length of follow-up	Average 1 year	Average 2.5 years
Endpoints of interest	Primary endpoint: First acute hospitalisations, Secondary endpoints: ED presentation, LTC admissions, mortality	Primary endpoint: First acute hospitalisations, Secondary endpoints: number of all acute hospitalisations, LTC admissions, all-cause mortality
Power calculations	Refer to text	Refer to text
**RCT**		
Eligibility criteria	Initially it was planned to recruit those from the Survey phase sample deemed most ‘vulnerable’ (to adverse outcomes) based on selection criteria employed in our ARCHUS study, including the number of medications prescribed.	Once the interRAI tool was chosen, interRAI based criteria were used to select residents, including triggering of 3 or more CAPS, (LTC institutionalisation risk) scores of 3 or more or at the discretion of the GNS. The number of medications reported in the interRAI tool included over-the-counter medications. On investigation, very few residents were being missed if number of medication criteria was dropped, so that inclusion criterion was removed. We retained from the ARCHUS study the validated criterion of the GNS’s impression of vulnerability/medical acuity.
Pre-randomisation checks	All eligible for the trial were to be checked by a study nurse before randomisation to ensure those no longer eligible for the trial were excluded from randomisation.	Survey phase recruitment issues meant that resources to conduct pre-randomisation checks were limited to database checks and short contact with residents in the active arm only, i.e. after randomisation.
Sample size	Refer to text	Refer to text
Timeline	We originally planned to complete the RCT in all villages by 28 Feb 2019	We completed RCT randomisation for in mid-January 2019 and completed the final MDT on 14 March 2019.
Interval between survey and randomisation	The interval between survey (and interRAI assessment) was anticipated as being 3 months, so the assessment would reasonably represent health status at time of randomisation.	An average interval of 9 months between survey and randomisation was achieved. Consequently, some assessments will misrepresent health status at time of randomisation.
Length of follow-up	Planned follow up possibly at 1, 2 & 4 years post-intervention.	Planned follow up 1.5 years post intervention MoH data. The 4th years post-intervention follow-up is conditional on obtaining additional funding
Endpoints of interest	Primary endpoint: First cute hospitalisation Secondary endpoints; All acute hospitalisations, LTC admissions, mortality	Primary endpoint: First acute hospitalisation Secondary endpoints: number of all acute hospitalisation, LTC admissions, mortality Power analyses are based on the primary outcome. We did consider changing the primary outcome to ED presentations, but decided against this as, in NZ, many people who are acutely hospitalised are not admitted via ED but go via GP referral to acute admitting units.
Power calculations	That residents were clustered into villages led to power calculations including an adjustment for a cluster effect.	Clustering was catered for by stratified random sampling, and adjustment for cluster effect was unnecessary.

##### Survey baseline

Recruited residents, after GNSs obtained their written, informed consent, were asked to complete a questionnaire facilitated by the GNSs that provided details of demographic, social engagement, and decision-making paradigms. Items in the resident survey included factors that influenced move to a RV, previous home ownership, home-based support services currently receiving, satisfaction in aspects of RV living, types and extent of social and physical activities currently undertaken, use of dental and other health care services, internet usage, loneliness, spiritual wellbeing and any planned surgery or medical intervention. This questionnaire was informed by our previous feasibility study [12]. Recruitment began in July 2016 and was completed in August 2018.

Where a prior interRAI Home Care (HC) (https://www.interrai.org/home-care.html) or Long Term Care Form (LTCF) (https://www.interrai.org/long-term-care-facilities.html) assessment had been completed within the past 6 months, this assessment was used. The purposes of an interRAI assessment is to accurately determine the characteristics of a person in order to fully describe their needs, ranging from clinical to social support. The outcome measures of the interRAI assessment are known as Clinical Assessment Protocols (CAPS) and are designed to assist the healthcare professional to interpret systematically all the information recorded [14].

We also utilised InterRAI-CHA as a component of assessment in the Survey phase, and for selection for the RCT. “the InterRAI CHA Assessment form is a Minimum Data Set (MDS) screening tool that enables an assessor to review multiple key domains of function, health social support and service use. Particular interRAI CHA items also identify persons who could benefit from further evaluation of specific problems or risks for functional decline. These items, known as triggers, link the interRAI CHA to the problem orientated CAPs. The CAPs provide general guidelines for further assessment and individualised care and services”.

##### Cohort study follow-up

Study outcomes will be to describe trajectories of healthcare utilisation. The primary outcome will be first acute hospitalisation, while secondary outcomes will number of all acute hospitalisations, LTC admissions and all-cause mortality. All are available from routinely collected Ministry of Health (MOH) administrative data, by use of each individual’s unique National Health Identifier (NHI). For any subjects declining entry into the RCT (below), GNSs confirmed their continued permission to obtain these centrally-held data.

##### RCT

Based on a combination of the interRAI assessment and selection criteria validated from our ARCHUS study [15] a sub-sample of resident from the baseline phase (initially estimated at about 28%) ‘at high risk’ of health and functional decline, will be selected for inclusion in the RCT (Table 1). These potentially ‘at risk’ residents, eligible for the RCT, will be identified by triggering three or more interRAI CAPS. There will be no additional exclusion criteria applied. After GNSs obtained written, informed consent, eligible residents will then be randomly allocated to the control or intervention arm, stratified by village. The randomisation list will be generated (using computer-based random number generation) by a statistician not involved in outcome measures. This will ensure that the two groups are balanced regarding each RV. The controls will receive no additional contact, assessments or services. The intervention group will receive a GNS-facilitated intervention plan, similar to our ARCHUS study [15]. In brief, this comprises a comprehensive geriatric assessment by a clinical team consisting of a GNS, a geriatrician and a clinical pharmacist reviewing baseline 1 assessments, residents’ medical records and a further update of health issues prior to the MDT meeting. If an urgent significant health issue is identified, intervention subjects will receive a direct referral from the research team to other relevant services and/or a phone call to the GP. Randomisation and MDTs began in March 2017.

The MDT review will occur in collaboration with the older person & their chosen support person(s), geriatrician or nurse practitioner, and clinical pharmacist. This will culminate in an MDT meeting (usually in the resident’s apartment) lasting approximately 45 min, to which the subjects’ general practitioners (GPs) will be invited. Treatment goals and recommendations will be discussed and developed with the resident and all present, and a summary of the MDT meeting with suggestions and recommendations sent by mail to each participant and their GP.

The effect of the intervention on health outcomes will be assessed by this RCT. Healthcare use (NZ Ministry of Health databases) using the resident’s unique NHI number will be evaluated 1-year pre and 1, 2- & 4-years post-intervention (the latter depending on further research funding being obtained). The Primary Outcome will be first acute hospitalisation. Secondary outcomes will comprise the number of all acute hospitalisations, LTC admissions, and all-cause mortality.

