### Power and sample size calculation

Initial power calculation for the RCT was performed prior to commencement of the Survey phase. Following commencement of the Survey phase it became apparent that the subjects were of higher medical acuity and vulnerability than we had anticipated and revised power calculations for the RCT were performed before RCT commencement.

Sample size for the Survey phase follow-up phases was largely governed by the sample needed for the RCT. An estimated 65% of the Survey phase follow-up residents were eligible for the RCT, meaning that 572 residents were needed in the Survey phase. An average of 2.5 years follow-up will be available for the Cohort phase by January 2020. If the rate of acute hospitalisation (primary outcome) is 55% per year we will have at least 80% power to show a 20% difference in the hazard ratio for any two categories.

For the RCT, we estimated 372 residents met the “high-risk” criteria, will be randomised and followed for 1 year after randomisation. The rate of acute hospitalisation in LTC residents is 67% per year (from previous work). We conservatively hypothesised the acute hospitalisation rate in the “high risk” RCT RV residents would be 70% per person-year. We would expect 80% power to show a 20% reduction in our primary outcome (acute hospitalisation). If the effect is stronger (e.g. 25% or 30% - as found in our ARCHUS [16] and ARCHIP [18] studies or longer follow-up, power will increase, though based on our earlier work (ARCHIP), the duration of any intervention effect may be under 1.4 years.

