### Statistical analysis

In the Survey phase, initial descriptive analyses will be conducted. Then, in both the Survey and Cohort phases, multivariate regression models (including logistic regression, log-binomial regression, linear regression and Cox regression) will be used to explore the influence factors on health outcomes adjusting for potential confounders (demographics, lifestyle, medical history, clinical characteristics, village characteristics etc.) and time to event when possible.

For the primary and main secondary outcomes in the RCT, analyses will be conducted on an intention-to-treat basis. Cox proportional regression models, with robust sandwich variance estimates, will be used to compare the time to health outcomes between the intervention and usual care groups. Hazard ratios (HRs) and 95% confidence intervals (CIs) will be calculated. Sub-group analyses will evaluate treatment effect for the main endpoint for different sub-groups, e.g. subgroup analyses for each endpoint by sex, large/small village, clinic/nurse/not, sampled/volunteers. Analyses will be conducted by a research statistician not involved in the clinical aspects of the study.

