### Study status

Recruitment to the Survey phase ended in August 2018**.** RCT randomisation was completed in mid-January 2019 and all MDTs were completed by 14 March 2019. This will give us, by end of January 2020, a median (range) 29 (18–42) months of Cohort follow-up and 18 (12–33) months RCT follow-up. Trial results will be the subject of further publications and communicated to residents by regular newsletters.

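### The RCT follow-up clock is stated inconsistently, as post-intervention in two places and after randomisation in another, and controls have no intervention date

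*Protocol article*

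**What the plan says.** The protocol article gives two starting points for RCT follow-up.

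- **Intervention.** The RCT section says that healthcare use "will be evaluated 1-year pre and 1, 2- & 4-years post-intervention". The implemented column of Table 1 (RCT, Length of follow-up) says "Planned follow up 1.5 years post intervention MoH data".
- **Randomisation.** Under Power and sample size calculation, eligible residents "will be randomised and followed for 1 year after randomisation".

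Other statements bear on the choice:

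- On the control arm, the RCT section says "The controls will receive no additional contact, assessments or services".
- On timing, Table 1 says "We completed RCT randomisation for in mid-January 2019 and completed the final MDT on 14 March 2019".
- Table 1 also says that pre-randomisation eligibility checks were cut back to database checks and "short contact with residents in the active arm only, i.e. after randomisation".
- Study status expects "18 (12–33) months RCT follow-up" by the end of January 2020, the first figure being the median.
- Statistical analysis says "For the primary and main secondary outcomes in the RCT, analyses will be conducted on an intention-to-treat basis". It specifies Cox models for time to outcome but does not name the date from which time is counted.

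**The concern.** A randomised time-to-event comparison needs one time origin that exists for everyone and is fixed by the allocation. The date of the MDT meeting is neither. Controls never have one, and the article assigns them no substitute date. An intervention resident has one only after remaining alive and in the trial through the interval between randomisation and the meeting.

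Followed to the letter, a post-intervention window would omit hospitalisations and deaths before the MDT in one arm only. Intervention residents who die or withdraw before the meeting would have no index date at all. During that interval the arms were also handled differently, because only the active arm was contacted. The 1-year pre-period, if it ended at the MDT, would contain time after randomisation in the intervention arm.

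What is at stake is the definition of the primary outcome window. An analysis plan written from the RCT section would start from a rule that cannot be applied to the control arm.

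**Working it through.** **1. The plan's own sample size, and the clock it uses.** Inputs from Power and sample size calculation: 70% in controls, a 20% reduction (so 56%), 80% power, 1 year after randomisation. Two-sided 5% and 1:1 allocation are assumed, as neither is stated. For two proportions,

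n per arm = [1.96·√(2·0.63·0.37) + 0.842·√(0.70·0.30 + 0.56·0.44)]² / 0.14² = 185.5, so 186.

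That gives 372 in total, the stated figure, with power 80.1%. It already rests on 1 year from randomisation. Whether a two-proportion calculation suits a Cox analysis is a separate question.

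**2. Which origin fits the stated follow-up.** Mid-January is taken as 15 January 2019, and the data cut as 31 January 2020.

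| From | To | Days | Months |
|---|---|---|---|
| Last randomisation | Data cut | 381 | 12.5 |
| Last MDT, 14 March 2019 | Data cut | 323 | 10.6 |
| Last randomisation | Last MDT | 58 | 1.9 |

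The stated minimum of 12 months fits the first row and not the second. The maximum of 33 months settles nothing: randomisation and MDTs both began in March 2017, which is 34 to 35 months before the cut.

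**3. The gap between randomisation and MDT.** Individual gaps are not given. A resident seen on 14 March 2019 had been randomised by mid-January, so that resident's gap was at least about 58 days. This says nothing firm about the rest of the arm. Gaps of 1 and 2 months are used below as assumptions.

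**4. What different applications would do when there is no treatment effect.** Constant hazard λ; gap g in years; 1-year window. λ = 0.70 if 70% is a yearly rate; λ = −ln(0.30) = 1.204 if it is a 1-year risk.

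(a) *Intervention clock starts at the MDT, with gap time and gap events both left out.* Under constant hazard the null hazard ratio stays at 1.0. Bias then needs selection before the MDT, or a hazard that changes with time. Neither can be sized from the documents.

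(b) *Time credited from randomisation, but only post-MDT events in residents event-free at the MDT counted.* With E = 1 − exp(−λ(1 − g)), the apparent rate ratio is E / [λ·(g + E/λ)]. For λ = 0.70 and g = 2/12, E = 0.442 and person-time = 0.167 + 0.631 = 0.798, so the ratio is 0.442 / (0.70 × 0.798) = 0.79.

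(c) *Intervention window from randomisation to MDT plus 1 year, control window 1 year.* Risk ratio = [1 − exp(−λ(1 + g))] / [1 − exp(−λ)]. For λ = 0.70 and g = 2/12, this is 0.558 / 0.503 = 1.11.

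| Quantity | λ = 0.70, 1 month | λ = 0.70, 2 months | λ = 1.204, 1 month | λ = 1.204, 2 months |
|---|---|---|---|---|
| First event before MDT, 1 − exp(−λg) | 5.7% | 11.0% | 9.5% | 18.2% |
| (b) apparent rate ratio | 0.89 | 0.79 | 0.87 | 0.76 |
| (c) apparent risk ratio | 1.06 | 1.11 | 1.04 | 1.08 |

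**5. Randomisation as time zero in both arms.** The distortions in (b) and (c) are both absent, and step 1 is unchanged.

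**The case against.** A reader might infer that the plan builds in immortal time that favours the intervention. The documents do not support that.

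- Nothing in the article sets different start dates by arm, excludes events before the MDT, or drops residents who never have one.
- The evidence on intent points to randomisation: the sample-size text, the 12-month minimum and the intention-to-treat commitment. The 1.5 years in Table 1 equals the 18-month median under Study status, so post-intervention may simply be loose wording for follow-up in the RCT.
- The ratios of 0.76 to 0.89 need a hybrid that the plan does not describe. A clock started cleanly at the MDT gives no bias under constant hazard, and another application biases the other way.
- The 10.6 months after the last MDT does not prove a missing 1-year window. End January 2020 is one data cut, and the RCT section foresees later follow-up.
- An article may leave time zero to an analysis plan that is not shown.

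All of this stands against a claim of actual bias. It does not remove the inconsistency. The point is not that the article is silent on time zero. It states two origins, and one of them has no meaning for the control arm. If randomisation is intended, the RCT section and Table 1 say something else.

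**Conclusion.** The time origin for RCT outcomes is contradictory, and the post-intervention version cannot be applied to controls. That conclusion rests on the wording and dates in the article and needs no assumption beyond reading mid-January as about the 15th.

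The risk of bias is conditional on how the wording is applied. Literal use would treat the interval before the MDT differently in the two arms and conflict with intention-to-treat. Its direction and size cannot be fixed from the documents. The ranges 0.76 to 0.89 (gap of 1 to 2 months) and 1.08 to 1.11 (gap of 2 months) are hypothetical illustrations. They assume constant hazard, no true effect and one common gap for the whole arm. They do show that the choice could matter on the scale of the 20% reduction the trial is designed to detect.

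**What to change.** - In the RCT section and in the implemented entry of Table 1 on length of follow-up, replace post-intervention with post-randomisation.
- In Statistical analysis, name the date of randomisation as time zero for both arms and for all RCT outcomes. State that every event from that date counts, including those before the MDT and those in intervention residents who never have one.
- Define the 1-year pre-period as the 12 months before randomisation in both arms.
- Carry the same definitions into the statistical analysis plan.

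The cost is wording only. Every trial resident has a randomisation date, and the outcomes come from routine Ministry of Health records in both arms. The sample size of 372 and the stated power do not change, because they already assume 1 year from randomisation.
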